## 2. Materials and methods

### 2.1. Study design

This is an exploratory cross-sectional observational study using VR technology to assess the performance accuracy of different hand gestures. An HMD will be used to immerse participants in the virtual environment. Motion trackers, attached to the hands and elbows, will provide participants with real-time upper body tracking (see section VR apparatus for more details). Data from the HMD and motion trackers will be continuously stored on a computer for analyses. We plan to recruit 60 schizophrenia patients and 60 age and gender matched controls over a 2-year period. The duration of the study is ~6 h. The assessments are separated into 2-h sessions/per day and all assessments are completed within a 72-h period.

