### 2.2. Participants

Schizophrenia patients will be recruited from the inpatient and outpatient departments of the University hospital of Psychiatry and Psychotherapy in Bern, Switzerland. All potential schizophrenia patients will be screened using the Mini International Neuropsychiatric Interview (37) for the DSM-5 criteria. Healthy controls will be recruited through advertisement and by word-of-mouth. Inclusion criteria for all participants include: right-handedness, 18–65 years of age, no substance abuse (except nicotine), and no history of neurological disorders or any other severe mental health disorders. Additionally, for controls only, no personal, or first-degree relatives with a history of any mental health disorders.

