## 3. Statistical analysis

Measurements collected from the tracking devices during gesture performance will be analyzed using linear mixed models. These will include upper body rotational data per gesture across all experimental blocks. Data are saved at a frequency of 60 Hz (16 ms). The rotational data between participants and the virtual agent performing the gestures will be compared across time based on distance metrics such as Dynamic Time Warping (DTW) that measures similarity between time series by considering the temporal relationship between rotational vectors. Group (patients and healthy controls) and gesture category (meaningless, intransitive, and transitive), as well as, their interaction will be added as fixed effects, while a single intercept parameter estimated for each participant will be added as random effects. Covariates in the model will also be considered if demographic characteristics such as age, gender or education are different between patients and controls. In addition, differences in symptom severity and motor deficits between inpatient and outpatient participants will also be considered. The Kruskal–Wallis test will be used to assess such differences. In addition, we will apply partial correlation analyses using the spearman method to examine the relationship between gesture performance accuracy in VR with symptom severity, motor, socio-cognitive and community functioning scores, while controlling for medication. This will help in determining if gesture performance accuracy using VR in patients is linked to a specific domain or is generalized across multiple domains.

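### Age and gender, the matching variables, enter the patient–control model only if the groups differ on them, so successful matching removes them; the cost is mainly a modest loss of precision

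*Protocol article*

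**What the plan says.** Section 2.1 gives the design and the matching: "We plan to recruit 60 schizophrenia patients and 60 age and gender matched controls over a 2-year period". Education is not a matching variable. Section 2.2 admits adults "18–65 years of age".

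Section 3 fixes what is always in the model: "Group (patients and healthy controls) and gesture category (meaningless, intransitive, and transitive), as well as, their interaction will be added as fixed effects". The random part is a participant intercept only: "a single intercept parameter estimated for each participant will be added as random effects". There is no term for matched pairs or matching strata.

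Demographic variables come in through a conditional rule: "Covariates in the model will also be considered if demographic characteristics such as age, gender or education are different between patients and controls". The article does not say how a difference is to be judged. A Kruskal–Wallis test is named shortly afterwards, but directly after the sentence on inpatients and outpatients, so it is unclear whether it also covers demographics. No threshold is given. No section of the article puts age or gender in the model unconditionally.

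**The concern.** The rule works against the design. Age and gender were chosen for matching, presumably because they were thought to bear on gesture performance. Successful matching makes the groups alike on both, and the rule then drops both. A covariate improves the precision of the group comparison to the extent that it predicts the outcome, whether or not the groups differ on it. With ages from 18 to 65, a relation between age and movement accuracy is plausible. Matching on a predictor and then omitting it also makes the group test conservative, because the model's standard error does not reflect the balance that the matching achieved.

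For education, which is not matched, the issue is different. The study is observational, so the groups may differ systematically, and a difference check with 60 per group can miss an imbalance of moderate size.

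At stake are the precision of the group main effect, which addresses the study's stated hypothesis, and some residual bias if a relevant imbalance goes unnoticed.

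**Working it through.** The article states no alpha, effect size, SD or power, so there is no figure of its own to reproduce.

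**Inputs from the article:** 60 patients and 60 controls; matching on age and gender (section 2.1); model terms and covariate rule (section 3).

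**Assumptions:** a correlation r between one participant-level covariate and a participant's mean accuracy; a two-sided 5% level for the imbalance check and the group test; a true group effect of 0.5 SD where power is shown.

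**1. Standard error of the group main effect.** Adjusted over unadjusted SE = √(1 − r²). Equivalent sample size = 120 / (1 − r²).

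| r | SE ratio | SE reduction | Equivalent participants |
|---|---|---|---|
| 0.1 | 0.995 | 0.5% | 121 |
| 0.2 | 0.980 | 2.0% | 125 |
| 0.3 | 0.954 | 4.6% | 132 |
| 0.4 | 0.917 | 8.3% | 143 |
| 0.5 | 0.866 | 13.4% | 160 |

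In simulation (20,000 runs per setting, no systematic imbalance), power with always adjusting against adjusting only if different was 79.4% v 78.0% at r = 0.2, 81.2% v 78.3% at r = 0.3 and 87.6% v 78.8% at r = 0.5.

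The interaction gains little. A covariate main effect is the same for all three gesture categories within a participant, so it cancels from within-participant contrasts.

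**2. Exact matching, matching variable omitted.** Simulated pairs at a nominal 5%:

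| r | Type I error, matching ignored | Power, matching ignored | Power, matching used |
|---|---|---|---|
| 0.2 | 4.3% | 78.0% | 78.6% |
| 0.3 | 4.1% | 78.9% | 80.8% |
| 0.5 | 2.3% | 81.3% | 88.1% |

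**3. Chance that the check finds a true imbalance d.** SE of the covariate difference = √(2/60) = 0.183 SD. The non-centrality is 0.3/0.183 = 1.64 or 0.4/0.183 = 2.19. With a t-test on 118 degrees of freedom, power is 37% for 0.3 SD and 58% for 0.4 SD.

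**4. Bias left by the rule at r = 0.4.** The check stays silent when the observed difference lies within ±1.96 × 0.183 = ±0.358 SD. By the truncated normal, the mean observed difference in those cases is d − 0.183 × [φ(b) − φ(a)] / [Φ(b) − Φ(a)], where a and b are the standardised limits.

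- d = 0.3: b = 0.317, chance of a miss 0.624. Mean difference = 0.3 − 0.183 × 0.379/0.624 = 0.189. Bias when missed = 0.4 × 0.189 = 0.076 SD. Averaged over the rule = 0.076 × 0.624 = 0.047 SD.
- d = 0.4: b = −0.231, chance of a miss 0.409. Mean difference = 0.4 − 0.183 × 0.388/0.409 = 0.226. Bias when missed = 0.4 × 0.226 = 0.091 SD. Averaged = 0.091 × 0.409 = 0.037 SD.

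The averages count adjusted cases as unbiased. A simulation of 20,000 runs at each d agrees: 0.077 and 0.092 SD when missed, 0.048 and 0.039 SD averaged.

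**The case against.** The strongest objection is that the harm is small and rests on figures the article does not contain. It gives no correlation between age or gender and accuracy. At r = 0.1 the gain is half a percent of the SE, and at r = 0.2 it is under two points of power. The study describes itself plainly: "This is an exploratory cross-sectional observational study using VR technology". The rule says covariates will be considered, which leaves room for judgement, and the detailed covariate list may stand in an analysis plan that is not shown. All of this lowers the severity. It does not rescue the rule: the article commits to a criterion, and that criterion runs against its own matching.

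Three stronger readings are tempting, and the documents do not support them.

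- **Bias of d × r.** A reader might take the uncorrected bias as 0.3 × 0.4 = 0.12 to 0.4 × 0.4 = 0.16 SD. That is the bias of never adjusting. Under this rule larger observed imbalances are caught, and those missed are smaller than average, which gives the lower figures above.
- **Serious confounding by age or gender.** The matching itself makes an imbalance of 0.3 to 0.4 SD in these two unlikely, and nothing in the article suggests that the matching fails. For them the cost is precision and a conservative test.
- **An invalid p-value because the model depends on a preliminary check.** For one covariate, simulated type I error of the conditional rule stayed at 4.5% to 5.7% in the settings examined, so this has little consequence.

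The 5% check is also an assumption, so the detection rates illustrate the rule and are not a property the article states.

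**Conclusion.** The point holds as a modest improvement in precision. Section 3 makes inclusion of the matching variables depend on a difference that the matching is meant to prevent, and nothing else in the article puts them back or models the matching. If age or gender predicts gesture accuracy, the group main effect is reported less precisely than the data allow and its test is conservative. The size depends wholly on the unknown correlation and is negligible at the lower end of the assumed range. The residual bias from a missed imbalance is small and concerns mainly education; its size rests on the assumed 5% check, imbalances and correlation. The finding does not imply an inflated false-positive rate or that the planned group comparison is unsound.

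**What to change.** In section 3, replace the conditional rule for age and gender with a statement that age (continuous) and gender are fixed effects in the primary mixed model whether or not the groups differ. State in advance that the group effect will be reported with and without education as a sensitivity analysis. Education should not simply be added to the primary model, because attained education may itself be affected by the illness. The primary estimate therefore stays open to an education imbalance, but the two results side by side show how much it matters.

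The cost is a sentence or two of text and two degrees of freedom. No new measurement is needed: age and gender must be known to match the controls, and the present rule already presupposes that education is recorded.

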## 1. Introduction

Schizophrenia is a complex mental health disorder that affects ~1% of the general population. Schizophrenia is characterized by a wide range of clinical symptoms including disorganized thinking, paranoia, hallucinations, motor abnormalities, executive dysfunction, social withdrawal and affective flattening, all of which greatly disturb social communication processes leading to poor community functioning and quality of life (1–3). Successful social communication is highly dependent on one's ability to correctly perceive, interpret and execute socially relevant cues (4). In recent years, gestures serve as an important research tool in understanding social communication deficits in schizophrenia patients (5, 6).

Gestures are biological movements used alone or in combination with speech, to aid in social communication (7). Video-recordings of gesture performance in clinical settings show that schizophrenia patients and individuals at high-risk for psychosis tend to use hand gestures less frequently, or in the wrong context (8–10) and spend significantly less time fixating on the performed gestures (11). In addition, schizophrenia patients have deficits in correctly imitating meaningless and meaningful gestures following visual demonstration from an experimenter. Errors include slow movements with reduced amplitudes, extra movements, omissions, and body-part-as-object (12, 13). These errors are associated with impairments in postural knowledge, tool use, and social perception, suggesting a generalized impairment in non-verbal social communication in schizophrenia (14). Furthermore, deficits in gesture performance predict poor community functioning (15), and are strongly associated with symptom severity, motor abnormalities, and executive dysfunction, such as processing speed, attention, and working memory abilities (5, 11, 13, 14, 16–23).

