### 2.6. Secondary outcomes

We will include additional non-verbal communication tasks outside of VR to assess participants' ability to recognize and perceive non-verbal social cues such facial expressions, biological movements, and voice tone. Motor, cognitive and community functioning domains will be assessed using well-established standardized rating scales and symptom severity and antipsychotic medication usage in all patients will also be accounted for. All clinical, motor, socio-cognitive and community functioning assessments can be found in Table 2.

**Table 2 T2:** Clinical, motor, socio-cognitive and community functioning assessments of participants.

**Secondary outcomes**	**References**

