**Socio-cognitive assessments**	
Biological motion	(48, 49)
Dot counting task	(50, 51)
EMOREC-B	(52)
Hinting task	(53)
MATRICS consensus cognitive battery	(54)
Postural knowledge test	(55)
Profile of nonverbal sensitivity	(56)

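### The planned correlations control only for medication and group general and social cognition in one domain, so they cannot show whether a social-task link is carried by general cognition

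*Protocol article*

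**What the plan says.** Section 3 (Statistical analysis) of the protocol article plans partial Spearman correlations to "examine the relationship between gesture performance accuracy in VR with symptom severity, motor, socio-cognitive and community functioning scores, while controlling for medication". It states the purpose as deciding whether accuracy in patients is tied to one particular domain or spread over several. No other control variable is named for this analysis.

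Table 2 sets out the domains. Under the heading "Socio-cognitive assessments" it lists seven instruments: biological motion, dot counting, EMOREC-B, the hinting task, the "MATRICS consensus cognitive battery", the postural knowledge test and the "Profile of nonverbal sensitivity".

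Section 2.6 first introduces tasks that "assess participants' ability to recognize and perceive non-verbal social cues such facial expressions, biological movements, and voice tone". In the next sentence it says: "Motor, cognitive and community functioning domains will be assessed using well-established standardized rating scales". There cognition appears as a domain of its own. The section's last sentence, Table 2, Section 3 and the hypothesis at the end of the Introduction all use the combined term.

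The Introduction also reports that gesture deficits are strongly associated with "executive dysfunction, such as processing speed, attention, and working memory abilities".

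**The concern.** The domain is the unit of the conclusion in Section 3, so the conclusion can be no finer than the domains and the control variables allow. A link found in the socio-cognitive domain could reflect general cognition, perception of social cues or knowledge of postures.

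General cognition is a competing explanation that the article itself raises, through the correlates cited in the Introduction. The task design makes it plausible too. Section 2.4 has participants watch a gesture and wait for a light to go off before imitating it, so some attention and retention is needed.

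At stake is the reading of the secondary correlations. A social-perception task may correlate with gesture accuracy only because both follow general cognition, and with medication as the sole control nothing in the stated analysis would reveal this.

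**Working it through.** The article gives no alpha, power or effect size for these correlations, so there is no figure of its own to reproduce. The calculation below illustrates how large the effect could be.

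**From the document:** 60 patients (Section 2.1); partial Spearman correlation with medication as the only control (Section 3).

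**Assumed:** two-sided 0.05; gesture-cognition correlation a = 0.3 to 0.5; social task-cognition correlation b = 0.4 to 0.6; no direct link between social task and gesture; medication unrelated to the other variables.

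**Step 1, implied correlation.** With no direct link, r = a × b, which runs from 0.3 × 0.4 = 0.12 to 0.5 × 0.6 = 0.30.

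**Step 2, chance of significance as planned.** Fisher's z for a rank correlation with k controls has SE = √(1.06/(n − 3 − k)). For n = 60 and k = 1, SE = √(1.06/56) = 0.1376. With m = atanh(r)/SE, the probability is 1 − Φ(1.96 − m) + Φ(−1.96 − m). For a = 0.4 and b = 0.5: r = 0.20, m = 0.2027/0.1376 = 1.473, probability 31.4%.

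**Step 3, cognition also partialled out.** If the cognitive score were error-free, the numerator is ab − ab = 0 and the probability is the nominal 5%. If the battery correlates 0.9 with general cognition, the partial correlation is (ab − 0.81ab)/√((1 − 0.81a²)(1 − 0.81b²)). For a = 0.4 and b = 0.5 this is (0.200 − 0.162)/√(0.8704 × 0.7975) = 0.038/0.833 = 0.046. With k = 2, SE = √(1.06/55) = 0.1388, m = 0.329, probability 6.2%.

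| a | b | r = ab | Significant, medication only | Partial r, battery added (0.9) | Significant, battery added |
|---|---|---|---|---|---|
| 0.3 | 0.4 | 0.12 | 14.2% | 0.025 | 5.4% |
| 0.4 | 0.5 | 0.20 | 31.4% | 0.046 | 6.2% |
| 0.5 | 0.5 | 0.25 | 45.9% | 0.060 | 7.1% |
| 0.5 | 0.6 | 0.30 | 61.4% | 0.076 | 8.5% |

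**Step 4, cross-check.** Simulation of 1,500 studies per setting, with the battery at 0.9, gave 31% falling to 7% for a = 0.4, b = 0.5, and 45% falling to 8% for a = b = 0.5. The formula runs slightly low after adjustment, so the top of the adjusted range may lie a little above 8.5%.

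The excess comes from the missing control. Splitting the Table 2 heading alone would change none of these percentages. It would only make a link with the battery readable as a cognitive one.

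**The case against.** The strongest reply is that the socio-cognitive label is an umbrella for social plus cognitive. On that reading Section 2.6 and Table 2 do not contradict each other, and the label is coarse but not wrong. Section 3 asks about broad domains, and separating social from general cognition is arguably a further question. The study calls itself exploratory, and a condensed article may leave score-level detail to a fuller document. The assumed correlations come from outside the documents. All of this lowers the weight of the point. It does not remove it, because Section 3 itself states the specificity question, the domains and the one control variable.

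A reader might infer three stronger things that the text does not support:

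- **That the scores are pooled.** No composite is defined, Section 3 speaks of scores in the plural, and Table 2 lists each instrument on its own line. Correlated one by one, a link with the cognitive battery would be visible under its own name. The working above assumes this separate analysis.
- **That a cognitive link will be reported as a social one.** Nothing in the article says so. It is a possible reading of a result, not a stated intention.
- **That the case for therapy depends on this grouping.** The Discussion and Conclusion make that case conditional on the VR measurement succeeding, and the intervention envisaged uses motor learning. The split between social and general cognition plays no part in it.

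Adjustment also has a real drawback. If social and general cognition overlap in substance, partialling out the battery may remove part of a true social link. The adjusted result should therefore not be the sole test.

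**Conclusion.** The point holds in a limited form. As described, the correlations cannot separate a social-task link from one carried by general cognition, and this bears directly on the specificity question that Section 3 sets. For one social task with no link of its own, the chance of a significant correlation is about 14% to 61% as planned. With the cognitive score added it is 5% if that score is error-free, and about 5% to 9% by formula if it correlates 0.9 with general cognition. These figures rest on the assumed correlations, 60 patients and a 0.05 level, none of which except the sample size is given in the article. The article also does not say what the cognitive battery measures beyond its title. This is an inexpensive improvement to a secondary, exploratory analysis. It does not affect the primary group comparison.

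**What to change.** In Section 3, with Table 2 arranged to match:

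1. Report general cognition (the cognitive battery) separately from the social-perception tasks (biological motion, EMOREC-B, hinting task, nonverbal sensitivity) and from the postural knowledge test. The sponsor should say where the dot counting task belongs, since the article does not.
2. Report the social-perception correlations twice: controlling for medication as planned, and with the overall score of the cognitive battery added to the partialled variables.
3. Judge domain specificity from both sets of results together, without requiring that a link survive adjustment.

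The cost is a few words and one degree of freedom. By the same approximation, the correlation detectable with 80% power moves from tanh(2.802 × 0.1376) = 0.367 to tanh(2.802 × 0.1388) = 0.370. The battery is already being collected. The remaining downside is possible over-adjustment where social and general cognition overlap, which is why both versions should be shown.

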To our knowledge, no study to date has utilized VR to examine accuracy of hand gestures in schizophrenia patients. To this end, the aim of the present study is to apply VR technology to collect measurements of naturally occurring hand gestures during an imitation task in schizophrenia patients and compare their performance to healthy controls. Additionally, we will administer motor, socio-cognitive and community functioning assessments used in previous research from our lab to determine their relationship with hand gesture accuracy in VR. In accordance with previous studies (5, 13, 14, 20), we hypothesize that schizophrenia patients will perform the required gestures less accurately than healthy controls and that these deficits will be linked to their psychopathology, motor abnormalities, as well as compromised socio-cognitive and community functioning.

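### The partial correlations control for medication only, so shared dependence on age among patients aged 18 to 65 could pass for a link between gesture accuracy and motor, cognitive or functioning scores

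*Protocol article*

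**What the plan says.** All places are in the protocol article.

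- **Hypothesis (Introduction).** Patients are expected to perform gestures less accurately than controls, and "these deficits will be linked to their psychopathology, motor abnormalities, as well as compromised socio-cognitive and community functioning".
- **Analysis of the links (3. Statistical analysis).** "we will apply partial correlation analyses using the spearman method", relating VR accuracy to symptom severity, motor, "socio-cognitive and community functioning scores, while controlling for medication". The stated purpose is to learn whether "gesture performance accuracy using VR in patients is linked to a specific domain or is generalized across multiple domains".
- **Demographic covariates (3. Statistical analysis).** "Covariates in the model will also be considered if demographic characteristics such as age, gender or education are different between patients and controls". This sentence directly follows the fixed and random effects of the linear mixed model and comes before the correlations are introduced.
- **Sample (2.1 and 2.2).** "We plan to recruit 60 schizophrenia patients and 60 age and gender matched controls over a 2-year period". The eligible range is "18–65 years of age".
- **Limitations (section 6).** Antipsychotic medication is again named as a covariate; age is not.

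**The concern.** A partial correlation removes only what is put in its control set. Age can plausibly affect how closely a person reproduces a demonstrated movement. It can also affect parkinsonism and retardation ratings, cognitive test performance and community functioning. If it affects both sides of a correlation, the two sides will correlate even when neither bears on the other.

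The safeguards elsewhere in the plan do not reach this analysis. Matching balances age between patients and controls but leaves the spread of age among patients untouched. The covariate rule depends on a difference between groups, which matching makes unlikely for age, and it concerns a different model.

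What is at stake is the interpretation the analysis was designed to give. A common cause such as age tends to produce links in several domains at once, and the plan would read that pattern as generalized.

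**Working it through.** The article states no alpha, effect size or correlation for this analysis, so there is no figure of its own to reproduce. The check asks how often a link would be declared when none exists once age is held fixed.

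**Inputs from the article.** 60 patients (the purpose sentence refers to patients); partial Spearman; one control variable, medication; ages 18 to 65.

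**Assumptions.** Two-sided test at 0.05; age uniform on 18–65; age correlates a with gesture accuracy and b with the clinical score; the two are unrelated given age; medication unrelated to age, except in step 5.

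**Step 1: induced correlation.** With medication unrelated to the other variables, the medication-only partial correlation is about r = a × b. For a = b = 0.4, r = 0.16.

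**Step 2: critical value.** Degrees of freedom are n − 2 − k, where k is the number of control variables. With k = 1 this is 60 − 2 − 1 = 57. The critical |r| is t/√(t² + df) = 2.002/√(2.002² + 57) = 0.256.

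**Step 3: rejection rate by Fisher's z.** The standard error is 1/√(n − k − 3) = 1/√56 = 0.134, and atanh(0.256) = 0.262. For a = b = 0.4, atanh(0.16) = 0.161, so the upper tail begins at (0.262 − 0.161)/0.134 = 0.75. That gives about 23%, and the lower tail adds about 0.1%.

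**Step 4: simulation of the partial Spearman test** (3,000 to 6,000 runs per setting, n = 60):

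| Age with gesture / score | a × b | Rejection, medication only | Rejection, medication + age |
|---|---|---|---|
| 0.2 / 0.2 | 0.04 | 6% | about 5% |
| 0.1 / 0.5 | 0.05 | 6–7% | about 5% |
| 0.2 / 0.4 | 0.08 | 9% | about 5% |
| 0.3 / 0.3 | 0.09 | 10% | 4–5% |
| 0.2 / 0.5 | 0.10 | 11.5% | about 5% |
| 0.3 / 0.5 | 0.15 | 19–21% | about 5% |
| 0.4 / 0.4 | 0.16 | 21–22% | about 5% |
| 0.5 / 0.5 | 0.25 | 45–47% | 4–5% |

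The step 3 approximation gives about 23% for the 0.4 / 0.4 row, close to the simulated 21–22%.

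**Step 5: can medication stand in for age?** Suppose medication correlates c = 0.3 with age and is linked to the two measures only through age. For a = b the partial correlation becomes a²(1 − c²)/(1 − c²a²). At a = 0.5 this is 0.25 × 0.91/(1 − 0.09 × 0.25) = 0.233, against 0.25 before. The simulated rejection rates at 0.3, 0.4 and 0.5 are 9%, 19% and 43%. Controlling for medication therefore removes little of the age effect.

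**Step 6: price of adding age.** With k = 2, df = 56 and the critical |r| is 0.259. With gender as well, df = 55 and it is 0.261.

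**The case against.** **The size rests on assumed correlations.** This stands. Nothing in the article says how strongly age relates to imitation accuracy or to any scale. The inflation depends on the product of two correlations, so it is small whenever either is weak: about 6–7% at 0.1 / 0.5. Large inflation needs both to be substantial.

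**A reader might multiply a rate by the number of scales.** The four domains in the correlation sentence hold 3 + 5 + 7 + 4 = 19 instruments in Table 2, and a count of expected false positives could be drawn from that. The article does not support such a count. It would give every scale the same age correlation, including the three psychopathology scales, for which no age mechanism is evident.

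**A link carried by age is still a real association.** True as far as it goes. The study is labelled exploratory and cross-sectional, and these are secondary outcomes. The fault lies in interpretation, but interpretation is the declared purpose of the analysis, and an exploratory label does not separate shared ageing from a generalized deficit.

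**A condensed article may leave covariates to the full plan, and some scores may be age-corrected.** The article does not leave this open: it names the control set and again names only antipsychotic medication under Limitations. Whether scores are age-corrected is not stated. Correction would weaken the effect for those scores.

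**Adjusting for more variables can do harm.** This stands for education, which may partly reflect illness or cognitive ability; removing it could remove real signal. No calculation here supports compulsory adjustment for gender or education.

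**Conclusion.** The concern holds for age. As written, the correlations that carry the second hypothesis leave age uncontrolled among patients, and neither the matching nor the covariate rule for the group model corrects this. The effect is negligible if age correlates about 0.2 with both measures, or if either correlation is near 0.1. It is modest at 0.3 (10%) and serious from about 0.4 upward (21–22%, then 45–47% at 0.5). These rates assume 60 patients, a two-sided 5% test, no link given age, and scores that are not already age-corrected.

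A reader might infer that ageing will produce false links here, or that a generalized finding would be an artefact. The article supports neither: it shows that this could happen and that the planned analysis could not tell. The point merits a change because the remedy is cheap and bears directly on the conclusion; it does not call the group comparison into question.

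**What to change.** In the Statistical analysis section, state that the partial Spearman correlations are computed within patients, with age and medication in the control set of every one, whether or not patients and controls differ in age. Report the medication-only result beside each, so that a reader can see how much of a link age accounts for. Say which scores, if any, are already age-corrected.

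Gender may be added to the control set at little cost. Education should appear only as a sensitivity analysis, for the over-adjustment reason given above.

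The cost is a line or two of wording and one degree of freedom out of 57, or two with gender. No new data are needed: the plan already compares age, gender and education between the groups.
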